## Abstract

**Background:**

The prevalence of type 2 diabetes mellitus (T2DM) is increasing worldwide. Digital interventions that incorporate the use of mobile phones and wearables have been getting popular. A combination of a digital intervention with support from professional management can enhance users’ self-efficacy better than a digital intervention alone and provide better accessibility to a lifestyle intervention. However, there are limited studies exploring the feasibility and efficacy of applying a digital intervention in Muslim-majority countries, and none have been conducted in Brunei Darussalam.

**Objective:**

The study aims to determine the effectiveness and feasibility of a proposed 16-week digital intervention program for T2DM self-management and to guide the rollout of a mobile app as part of a population health solution for adults with T2DM in Brunei. The primary outcome of this study is to measure the proportion of participants with a hemoglobin A_1c_ (HbA_1c_) reduction of at least 0.6% from baseline, and the secondary outcomes include a change in HbA_1c_, BMI, lipid profile, and EQ-5D-5L score.

**Methods:**

This single-arm nonrandomized pilot study will recruit participants using web-based (with the national health care app [BruHealth] and official social media platforms being used for outreach) and offline (in-person recruitment at health centers) approaches. A target of 180 individuals with T2DM aged between 20 and 70 years that meet the inclusion criteria will be enrolled in a 16-week digital intervention program. Baseline and postintervention markers will be evaluated.

**Results:**

The study received approval from the Medical and Health Research & Ethics Committee of the Brunei Darussalam Ministry of Health (MHREC/MOH/2022/4(1)). The recruitment process is ongoing, and we anticipate that the study will conclude by April 2023. This will be followed by data analysis and the reporting of outcomes with the intention to publish. The results of this study will be disseminated through scientific publications and conferences. This study will serve as a guide to launch T2DM digital therapeutic programs and extend to other noncommunicable diseases (NCDs) if proven as an effective and feasible approach in Brunei.

**Conclusions:**

The Development and Exploration of the Effectiveness and Feasibility of a Digital Intervention for Type 2 Diabetes Mellitus (DEsireD) study will be the first study to investigate the clinical effectiveness and feasibility of the proposed 16-week T2DM digital intervention program tailored for Brunei, a Muslim-majority country. The findings of this study can potentially scale up the proposed model of care to other NCDs as a national approach for health management solutions.

**Trial Registration:**

ClinicalTrials.gov NCT05364476; https://clinicaltrials.gov/ct2/show/NCT05364476

**International Registered Report Identifier (IRRID):**

DERR1-10.2196/43208

## Introduction

### Background

The worldwide prevalence of diabetes continues to increase, and the International Diabetes Federation (IDF) estimates the global prevalence of diabetes currently to be 9.1% with Brunei Darussalam reported to be at 12.4% among the 20-75 years old age group [1]. Type 2 diabetes mellitus (T2DM) is associated with a decreased quality of life (QOL) and increased mortality [2] and economic burden on individuals, families, and society in general [3]. Diabetes and its related complications can have devastating costs to health care systems and the national economy. According to IDF Diabetes Atlas, the global health care expenditure for the management of diabetes and diabetes-related complications was approximately US $850 billion in 2017 and is expected to increase to US $958 billion in 2045 [4].

Lifestyle interventions and modifications can effectively reduce the risk of diabetes-related complications. The American Diabetes Prevention Program [5], the Finnish Diabetes Study [6-8], and the UK DiRECT (Diabetes Remission Clinical Trial) study [9] have shown that in various populations lifestyle interventions can delay the development of T2DM and related cardiovascular complications. Lifestyle interventions remain crucial in the management of a patient with chronic disease. These interventions are traditionally performed through an in-person, face-to-face outpatient visit; such means of engagement are often plagued with challenges and often difficult to administer in the outpatient setting due to resource limitations [10,11]. The combination of offline outpatient care with a web-based software remote management model has proven to be effective in recent years [9], providing opportunities to explore further digital interventions.

Accelerated by COVID-19, digital interventions, which use different digital and mobile technologies to support health system needs, have been gaining popularity [11]. They have been shown to be safe and cost-effective in achieving positive health outcomes for T2DM [12,13]. Results from two 2020 systematic reviews and meta-analyses have shown that mobile health interventions (eg, mobile phone SMS text messages, smartphone apps, wearables, portable monitoring devices, or web-based coaching) can significantly improve hemoglobin A_1c_ (HbA_1c_) with a standardized mean difference of –0.44 [14] and a weighted mean difference (WMD) of –0.4 when compared with traditional treatment and a fasting blood glucose WMD of –0.52 [15]. A more recent systematic review in 2022 has also revealed an overall improvement in HbA_1c_ (–0.9%) compared with usual care for T2DM [16]. Digital interventions have also been used to reduce BMI and waist circumference by 1.7 kg/m^2^ and 5.77 cm, respectively [17]. On the contrary, digital interventions did not demonstrate improvement in total cholesterol, low-density lipoprotein cholesterol, or triglyceride levels [17].

Despite the proven effectiveness of digital interventions in the management of T2DM in adults, there are limited studies exploring the feasibility and efficacy of applying digital interventions in Muslim-majority countries, and no studies have been conducted in Brunei, whose population is 82.1% Muslim [18].

### Rationale of Study

This study will attempt to address the resource limitations in providing lifestyle management tools to patients with chronic diseases, specifically T2DM, by providing an adaptable and easily accessible platform to administer digital lifestyle interventions in combination with offline support.

This study is a single-arm nonrandomized clinical trial, which is the first study being conducted in Brunei to assess the potential effectiveness and feasibility of using a digital intervention for participants with T2DM. In this study, the digital intervention for participants includes the use of a mobile phone, wearable devices, and hardware to collect participants’ health information and provide telehealth consultation by health coaches based on the collected information. Through an integrated online and offline model of management, this digital intervention aims to improve diabetes management for patients in an outpatient setting. This intervention will allow accessibility to nonpharmacological lifestyle treatments outside of the hospital with the long-term goal of improving QOL and decreasing mortality, morbidity, and the economic burden of diabetes on health care resources.

### Aims and Objectives of Study

The study is conducted with the following aims: to assess the potential effectiveness and feasibility of a comprehensive digital intervention for people with T2DM, to explore the effects of a combined online and offline intervention for the management of T2DM, to improve the accessibility of a lifestyle intervention among participants with T2DM, and to understand the process of guiding the rollout of an app for T2DM management as part of a health management digital solution [19].

The primary objective is to investigate the proportion of participants with a decrease in HbA_1c_ of 0.6% through lifestyle modifications using a digital intervention after 16 weeks. Secondary objectives include estimating the change in HbA_1c_ and BMI, improvement in lipid profile components at week 16, and change in QOL measured by the EQ-5D-5L compared with baseline measurements.

## Methods

### Study Design

This study is a single-arm nonrandomized clinical trial that will collect participants’ baseline data, apply relevant assessment scales, and collect data using a comprehensive digital intervention in 16 weeks to evaluate the improvement of relevant markers post intervention. Figure 1 provides the standard operating procedure of the Development and Exploration of the Effectiveness and Feasibility of a Digital Intervention for Type 2 Diabetes Mellitus (DEsireD) clinical trial.

**Figure 1 figure1:**
[figure not shown]
The DEsireD pilot trial study protocol. Bru-HIMS: Brunei Darussalam Healthcare Information and Management System; DEsireD: Development and Exploration of the Effectiveness and Feasibility of a Digital Intervention for Type 2 Diabetes Mellitus.

### Population

#### Inclusion Criteria

The study participants will need to meet all the following criteria: diagnosed with T2DM, HbA_1c_≥7% within 12 months prior to recruitment, age range between 20 and 70 years, and BMI between 23 and 50 kg/m^2^.

#### Exclusion Criteria

Individuals will be removed if they meet any of the following exclusion criteria: pregnant/breastfeeding; on insulin therapy or noninsulin injectable medication; a history of diabetes crisis (hypo- or hyperglycemia) in the past 6 months; blood pressure ≥160/100 mmHg; recurrent history of acute pancreatitis; decompensated liver cirrhosis; estimated glomerular filtration rate <60 ml/min/1.73 m^2^; a history of acute myocardial infarction or acute coronary syndrome (within the past 1 year), arrhythmias, or heart failure (New York Heart Association class II-IV); proliferative diabetic retinopathy; foot ulcer or gangrene; deep vein thrombosis of lower limbs (within the past 12 months); intermittent claudication; a history of cerebral hemorrhage or acute cerebral infarction (within the past 12 months); a history of active cancer; posttransplant/perioperative individuals (defined as planned for operation in the next 6 months); a history of hypo- or hyperthyroidism, including subclinical states; musculoskeletal injuries resulting in difficulty in performing physical activities; failure to provide consent; unable to perform activities of daily living; and unable to use WhatsApp and YouTube via mobile devices (eg, phone or tablet).

### Recruitment

Participants will be recruited using web-based and offline methods based on the inclusion and exclusion criteria.

#### Offline Recruitment

For offline recruitment, promotional posters and flyers will be used. These publicity materials will be placed at the front counters of health centers and in the main referral hospital (ie, the Raja Isteri Pengiran Anak Saleha [RIPAS] Hospital). Flyers will be actively given out by health coaches and recruitment teams at health centers; the flyers will be placed in the medication bags of the patients who collect oral diabetic medications from RIPAS Hospital.

#### Web-Based Recruitment

In addition to traditional on-site outreach via official social media approaches, a technology-assisted adaptive recruitment strategy was used for participant recruitment [20]. Sociodemographics, comorbidities, and medication lists were extracted from the Brunei national electronic medical record system (Brunei Darussalam Healthcare Information and Management System [Bru-HIMS]) for eligibility screening. A push notification for study invitation will be sent via BruHealth to identify eligible patients with T2DM. For users who choose to response to the nudge, they will be directed to a landing page with a questionnaire for them to fill in more required details (Figure 2). While this pilot aims to recruit 180 participants, the recruitment rate was low after 3 months. Therefore, a study invitation linking to the same questionnaire was sent via SMS text message. The recruitment banner to the same link can also be seen by any BruHealth users.

A total of 9990 potential individuals with T2DM who fulfilled the inclusion and exclusion criteria (except BMI due to data unavailability) were extracted from the Bru-HIMS database, and study invitations were sent via push notifications and SMS text messages.

**Figure 2 figure2:**
[figure not shown]
Push notification via the national health care app (BruHealth) for the Development and Exploration of the Effectiveness and Feasibility of a Digital Intervention for Type 2 Diabetes Mellitus (DEsireD) study recruitment.

### Participant Selection at Baseline

Potential participants will be seen by the health coaches at the health center, where informed consent will be signed by participants prior to undergoing the screening process (see the Data Collection, Management, and Analysis: Baseline Assessment and Endline Assessment sections). The clinical investigators will review the baseline blood test results and determine whether an individual satisfies the inclusion criteria.

### Intervention

Participants will be enrolled in a 16-week program that consists of online (web-based consultations and group education sessions) and offline support (baseline and endline assessments) from health coaches and a dietitian. Participants will be given a fitness band, smart weighing scale, and glucometer set to collect one’s health information. A diet and exercise recommendation based on their submitted food and exercise log and collected health data will be provided by health coaches. A lesson plan consisting of animations, videos, infographics, and articles will be given on a weekly basis with the intention to empower participants with diabetes self-management knowledge.

The 16-week program was crafted in collaboration with the expertise of a board-certified endocrinologist in Brunei, a registered dietitian, and a physiotherapist according to evidence-based guidelines and national guidelines [21-23]. The intention is to improve the outcome of diabetes care management by influencing the participant through various methods of information via knowledge empowerment.

To ensure the successful implementation of the study and that the designed education materials are able to meet the local context, the team has worked collaboratively with diabetes specialists from the Ministry of Health, Brunei Darussalam, to design the framework of this study, oversee the program, and provide advice regarding the contents of all educational materials. To meet the cultural needs of Muslim participants, education materials that specifically focus on managing T2DM during Ramadan were developed according to relevant studies and guidelines [23-26].

### Outcome Measures

#### Primary Outcome

The primary outcome will be the proportion of participants with a decrease in HbA_1c_ by 0.6% through lifestyle modifications via digital intervention after 16 weeks.

#### Secondary Outcomes

Secondary outcomes will include a change in HbA_1c_, BMI, lipid profile, and the EQ-5D-5L components at week 16 compared with baseline readings.

### Roles and Responsibilities in the Study

#### Health Coach

The main objective of a health coach is to facilitate an efficacious and effective lifestyle intervention for the participants. The responsibilities of the health coach include providing personalized nutrition and exercise recommendations for the participants in concordance with digital management to optimize the primary and secondary outcome measures; reviewing participants’ daily self-monitoring logs of blood glucose, weight, meals, and exercise on a weekly/biweekly interval; and adhering to the escalation pathway (see Escalation Pathway section) to ensure participants’ safety.

#### Dietitian

The dietitian will lead and provide training to the team the delivery of the diabetes self-management intervention in the study with the intention to ensure the competency level of health coaches. The dietitian will also engage and empower participants’ nutrition knowledge for self-managing T2DM with web-based support via small group education sessions and web-based consultations. The dietitian is required to adhere to the escalation pathway to ensure participants’ safety. Additionally, the dietitian will assist in the evaluation of the clinical trial effectiveness and outcomes according to the collected biometric data and blood test results.

### Study Withdrawal

The participant may withdraw from the trial at any time by withdrawing their informed consent. An end-of-study form will be given, and the reason for withdrawal will be documented.

### Statistical Analysis: Sample Size Calculation

A statistical power calculation was performed as follows: a sample size of 120 achieves 80% power to detect a proportion of 0.63 using a 1-sided exact test with a significance level of 0.025. These results assume that the proportion of the population under the null hypothesis is 0.5. Considering a dropout rate of 30%, the target sample size is 180.

### Data Collection, Management, and Analysis

#### Baseline Assessment

During the screening process at baseline, participants will undergo a panel of blood tests to determine eligibility for study participation. Baseline blood tests include full blood count, HbA_1c_, fasting blood glucose, fasting lipid profile, liver function test, renal panel, and thyroid function test. The clinical investigators will review baseline blood test results and determine whether potential participants satisfy the inclusion criteria. Eligible participants will be enrolled in the study, asked to complete the EQ-5D-5L questionnaire, provided with loaned devices, and requested to submit data required on a weekly basis at enrollment.

#### Study Assessment

During the 16-week study period, participants will be required to log their blood glucose levels, weight, and heart rate using the loaned devices into a daily report card. They will also be required to manually record their meals and exercise in the same report card. Reviews of logs will be performed on a weekly interval by the health coaches.

#### Endline Assessment

Upon completion of the 16-week intervention, participants will undergo a second panel of blood tests, which include full blood count, HbA_1c_, fasting blood glucose, fasting lipid profile, and liver function test as part of the primary and secondary outcome measures. Participants will also be asked to complete the EQ-5D-5L questionnaire to assess participants’ QOL in comparison to baseline.

#### Data Management

A dedicated proprietary research platform called EVYDResearch (EVYD Technology Sdn Bhd) will be used for data management. Data confidentiality will be maintained through EVYDResearch, as only the research team will have access to the full information. Sociodemographic and clinical variables will be extracted from Bru-HIMS and integrated into EVYDResearch. Data collected via questionnaires and diaries will be manually transcribed and housed in EVYDResearch. Physical copies of all the collected data, such as case report forms, informed consent forms, and questionnaires, will be locked in a cabinet that is only accessible to the research team. All data will be stored for 5 years and destroyed thereafter in compliance with the Ministry of Health, Brunei Darussalam regulations.

#### Statistical Analysis

Descriptive statistics will be performed for both primary and secondary outcomes. Frequency and count will be calculated for categorical variables. Means, SDs, and quartiles will be calculated for continuous variables. EVYDResearch will be used for simple data validation rules, such as uniqueness and missingness; descriptive statistical analysis for primary and secondary outcomes; and simple visualization plots. Additionally, R (R Foundation for Statistical Computing) or other software may be used when necessary to perform more advanced statistical analysis and data visualization.

### Event Safety Monitoring

The terms pertaining to events have been adapted from ClinicalTrials.gov [27] and are as follows:

Adverse Events are unfavourable changes in health, including abnormal laboratory findings, that occur in trial participants during the clinical trial. Serious Adverse Events include adverse events that result in death or result in either inpatient hospitalization or the prolongation of hospitalization, are life-threatening or result in a persistent or significant disability/incapacity. Other important medical events, based on appropriate medical judgment, may also be considered Serious Adverse Events if a trial participant's health is at risk and intervention is required to prevent an outcome mentioned. Other Adverse Events are adverse events that are not Serious Adverse Events but exceed the indicated frequency threshold.

All adverse events will be logged in the adverse events form. Any serious adverse events (expected/unexpected) will be reported to the Brunei Darussalam Medical and Health Research & Ethics Committee (MHREC) by the principal investigator within 24 hours of the event through the adverse events form.

For medical events, health coaches will review the weekly report card and follow the escalation pathway as described below.

### Escalation Pathway

#### Health Coach to Dietitian

Participants with poorly controlled capillary blood glucose (defined as blood glucose <4 mmol/L and >16.6 mmol/L) will be referred for web-based counseling by the dietitian.

#### Dietitian to Clinical Investigators

Participants with any of the following will be referred to the clinical investigators: two episodes of hypoglycemia, which is defined as a blood glucose of <4.0 mmol/L with or without symptoms of hypoglycemia, despite diet and lifestyle modifications, and more than 2 occasions of hyperglycemia, which is defined as a blood glucose of >16.6 mmol/L in a week.

#### Clinical Investigators to Diabetes Nurse Educators

In the respective clinic where participants see their primary physician for diabetes care, participants who require counseling about the timing of medications to meals and exercise will be referred to the diabetes nurse educators.

#### Consultations With Clinical Investigators

Consultations with clinical investigators will only be done via the virtual clinics (refer to Figures 3 and 4) that are specifically set up for this study period. Participants with recurrent hypoglycemia and hyperglycemia despite lifestyle modification will be excluded from the study for the participant’s safety. The clinical investigators will write a letter to inform the participant’s primary physician for an urgent review of their treatment. However, participants who do not experience any of the above issues will continue their routine clinic visits (if any) with their primary physician during the study period, and any changes in medications will be noted. Such changes in medication are allowed as part of participants’ usual care and do not constitute an exclusion from the study.

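### Enrolled participants are excluded from the study on post-baseline glycaemia, and on the natural reading they leave the HbA1c responder proportion: outcome-related selection of unknown direction and size

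*Protocol article*

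**What the plan says.** Under Consultations With Clinical Investigators, the Protocol article says: "Participants with recurrent hypoglycemia and hyperglycemia despite lifestyle modification will be excluded from the study", and gives safety as the reason. Participants without these problems carry on with routine care, and for their medication changes the same section says: "Such changes in medication are allowed as part of participants’ usual care and do not constitute an exclusion from the study". So the text itself sorts who is out of the study and who stays in.

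The preceding section, Dietitian to Clinical Investigators, lists the referral triggers: "two episodes of hypoglycemia, which is defined as a blood glucose of <4.0 mmol/L with or without symptoms of hypoglycemia", and "more than 2 occasions of hyperglycemia, which is defined as a blood glucose of >16.6 mmol/L in a week".

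The primary outcome is the "proportion of participants with a decrease in HbA_1c_ by 0.6% through lifestyle modifications via digital intervention after 16 weeks". The article does not state the denominator or how participants excluded under the safety rule are counted. Endline Assessment places the second HbA1c after completion of the 16-week intervention. The sample size section requires 120 participants for a one-sided exact test at 0.025 (null 0.5, alternative 0.63, power 80%) and adds: "Considering a dropout rate of 30%, the target sample size is 180".

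**The concern.** The exclusion takes place during the intervention, and its criterion is glucose control, the process that HbA1c measures. If those excluded are not counted, the analysed group has been selected on a variable related to the endpoint.

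Repeated readings above 16.6 mmol/L despite the programme suggest that HbA1c has not fallen much, so removing such people would tend to raise the responder proportion. Repeated readings below 4.0 mmol/L do not suggest failure, and removing those people could lower it.

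The responder proportion is the only analysis with a stated power. It is tested against a fixed value with no comparator arm, so nothing offsets a selection of this kind. The Conclusions say that the evidence is meant to guide a nationwide rollout.

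**Working it through.** **The plan's own figure.** With n = 120 and null 0.5, the smallest rejection threshold with a tail of at most 0.025 is 72 responders. The attained level is 0.0177 and the power at 0.63 is 0.782, close to the stated 80%. Enrolling 180 with 30% lost leaves 180 × 0.7 = 126. At n = 126 the threshold is 75, the attained level 0.020 and the power 0.816.

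**Does the design treat losses as non-evaluable?** If all 30% counted as failures and 0.63 of the rest responded, the overall proportion would be 0.63 × 0.7 = 0.441, below the null of 0.5. The calculation makes sense only if losses are left out of the proportion.

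**Size of the shift.** Let p be the true responder proportion among all otherwise evaluable participants, f the share excluded under the rule and q the proportion of the excluded who would have responded. Among those kept,

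p_obs = (p − f·q) / (1 − f).

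The protocol gives neither f nor q, so both are assumed. Take p = 0.50 (the null) and 126 evaluable before exclusions, and apply the exact one-sided 0.025 test to the number kept:

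- f = 5%: 126 × 0.95 ≈ 120 kept, threshold 72.
  - q = 0: 0.5/0.95 = 0.526, false success 6.3%.
  - q = 0.25: (0.5 − 0.0125)/0.95 = 0.513, false success 3.5%.
  - q = 0.5: 0.500, false success 1.8%.
- f = 10%: 126 × 0.90 ≈ 113 kept, threshold 68.
  - q = 0: 0.5/0.90 = 0.556, false success 18.6%.
  - q = 0.25: (0.5 − 0.025)/0.90 = 0.528, false success 6.9%.
  - q = 0.5: 0.500, false success 1.9%.

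**Mixed and opposite directions.** Here the start is 120, with 10% excluded, 108 kept and threshold 65:

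- Half hyperglycaemic (q = 0), half hypoglycaemic (q = 0.8): (0.5 − 0.05 × 0.8)/0.9 = 0.511, false success 3.6%.
- The same split with q = 1 in the hypoglycaemic half: (0.5 − 0.05)/0.9 = 0.500, no bias.
- All hypoglycaemic (q = 0.8): (0.5 − 0.08)/0.9 = 0.467, false success 0.3%, a downward bias.

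**Effect of keeping them as failures.** With n = 120, threshold 72 and 0.63 among the rest, the overall proportion is 0.63(1 − f):

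- f = 2%: 0.617, power 0.69.
- f = 5%: 0.599, power 0.53.
- f = 10%: 0.567, power 0.26.
- With no exclusions the power is 0.78.

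**The case against.** The strongest reply is that no sentence removes these participants from the denominator. The rule belongs to a safety pathway and gives safety as its reason. Analysis sets are commonly left to a statistical analysis plan, which is not shown here. Inflating for dropout allows for lost data; it does not declare a completers-only analysis. All of this is correct, so removal from the denominator is an inference. It is a strong one, because an excluded participant has no planned endline HbA1c, and a later analysis plan cannot supply a value that was never collected.

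A reader might go further and infer that the proportion is biased upward because nearly all those excluded would be non-responders. The article does not support that:

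- The rule names hypoglycaemia as well as hyperglycaemia.
- Entry requires HbA1c of at least 7% with no upper limit, and the endpoint is a fall of 0.6, not a target level. Someone starting very high could have repeated readings above 16.6 mmol/L and still respond.
- It is unclear whether the rule needs both conditions or either one. Requiring both would make exclusions rarer.
- No exclusion rate is given. Entry criteria already remove users of insulin or other injectables and anyone with a diabetes crisis in the past 6 months, so large shares have no basis in the text.

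The illustration also takes exclusions on top of the 30% dropout, although they may be part of it.

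**Conclusion.** The point holds as a risk of outcome-related selection in the primary proportion. A demonstrated upward bias is not established. The article states the exclusion, its post-enrolment timing and its link to glycaemia. That those excluded then leave the analysis follows from the endline timing and the sample size logic, but is not written.

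The size depends on two quantities that the article does not give. If 5% to 10% were excluded, the chance of false success would be 6.3% to 18.6% with no responders among them and 3.5% to 6.9% with a quarter responding, against an attained 2.0% with no exclusions. If half of them would respond there is no bias, and above that the trial understates the response. In either direction the remedy is the same, and it is worth making because this is the only powered analysis.

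**What to change.** Leave the clinical safety rule unchanged and alter only its consequence for the data:

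- Reword exclusion from the study as stopping the programme while remaining in follow-up and in the denominator of the primary analysis.
- Obtain the week-16 HbA1c at the endline visit or from Bru-HIMS, which already feeds the study database, and use it in the primary analysis. Count those in this group with no value as non-responders.
- As sensitivity analyses, (a) count values obtained after the urgent treatment review as non-response, and (b) report the proportion without these participants. The first belongs among the sensitivity analyses because the protocol keeps other participants in the study when their medication changes.
- Report the number excluded by reason, hypoglycaemia or hyperglycaemia.
- Have the investigators clarify whether the rule requires both conditions or either, and reconcile it with the referral triggers.

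The cost is a wording change, a records look-up, and a headline proportion and power that may be lower. The loss is not necessarily small: if 2% or 5% were excluded and all counted as failures, power at n = 120 would fall from 0.78 to 0.69 or 0.53. Retrieving actual HbA1c values limits that loss wherever some of these participants did respond.
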